For primary tumor and metastatic tissues, a hematoxylin and eosin section of FFPE sample will be assessed by the pathologist, with the aim of selecting areas of tumor with >70% cellularity. Two unstained sections will be macrodissected and processed for both DNA extraction using the QIAamp DNA FFPE Tissue Kit (Qiagen) and RNA extraction using the RNeasy FFPE kit (Qiagen). Somatic mutations will be assessed by targeted deep sequencing applied to plasma DNA (cfDNA test), tumor DNA (sDNA test) and, CTC-DNA (ctcDNA test). For each patient, genomic DNA from normal peripheral blood leukocytes will be assayed. Fully customized amplicon-based assays will be used to include genes of the ER/PR, HER2, PI3K/AKT1/mTOR, and MAPK pathways, and CDK 4/6 activation. The somatic mutation profile of the DNA extracted from all samples will be assessed according to the techniques developed as proof of concept by Forshew [20], Dawson [19], and Mutarza [22]. Structural variants of DNA will be assessed by applying the copy number variation (CNV)/CNV-FFPE nCounter Analysis System. RNA will be assayed for the PAM-50 expression profile to determine the subtype of breast cancer in the primary tumor, while the metastatic tissue and CTCs will be analyzed using the nCounter Analysis System.

Blood collected in ethylenediaminetetraacetic acid tubes will be processed within one hour to separate plasma, WBCs, and CTCs. Samples will be frozen at -80ºC until the nucleic acids extraction is scheduled. Following the method described by Dawson et al [19], DNA will be extracted from plasma using the QIAamp Circulating Nucleic Acid kit (Qiagen). The total amount of cfDNA will be quantified using previously described methods [19,23]. After collection of plasma, the remaining buffy coat-containing WBCs will be removed. DNA will be extracted using adsorption methods. Peripheral blood mononuclear cells will be obtained from blood by density gradient centrifugation, which will then be mixed with CTC beads and loaded onto a microfluidic cartridge following the ISOFLUX-CTC procedures (Fluxion Biosciences Inc). Enriched CTCs will be processed for enumeration or be stored for further DNA and RNA extraction.

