### Sample Size and Statistical Analyses

Analyses of genomic DNA sequencing data are considered exploratory in nature, and will generate new hypotheses. For this study, we have estimated that three patients per month will be enrolled, reaching a final sample size of 40 patients with complete data to proceed for further analyses.

According to Hart et al [24], a sample size calculation comparing two groups involves five factors, namely (1) the depth of sequencing and consequent expected count for a given transcript, (2) the coefficient of variation of counts within each of the two groups, (3) the fold-change that we wish to detect, (4) the target false positive rate and the false negative rate, and (5) the sample size in each group. Setting 3000x as the sequencing depth and 0.4 as the coefficient of variation, we estimate there is enough statistical power (80%) to detect effects higher than 1.29.

Clinical and demographic characteristics of patients will be described using descriptive statistical methods. Univariate analysis will be performed in order to describe the distribution, central tendency, and dispersion of the variables. Bivariate analysis will be used to find relationships between different variables. Analyses will be performed using the Statistical Package STATA version 12.1 or the newest version of R, according to the requirements of the analyses. Additionally, a scoring algorithm will be established in order to compare the mutation/CNV status in cfDNA/CTC-DNA against primary tumors, metastases, and germinal line DNA.

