The genome sequencing data will be analyzed using bioinformatics tools. Sequencing reads will be aligned to the human reference genome building hg38 (GRCh38) to generate a list of potential genomic variations through variant-calling procedures. The alignments will be run using tools based on the Burrows-Wheeler Transform such as Burrows-Wheeler Aligner or Bowtie2. The aligned results will be processed using the SAMtools suite in order to obtain sorted, indexed, and binary files. If necessary, duplicate reads will be marked with Picard and removed before single nucleotide variation (SNV) identification with softwares such as SAMtools, mpileup, and MuTect. These programs will be used to detect low-frequency variants, as data cannot be expected to follow normal ploidy models. Additional steps will be performed if needed, such as the recalibration and realignment using BaseRecalibrator and IndelRealigner, both in the GATK suite. In recent years, a number of important algorithms and implementations have been designed for specific SNV detection tasks in matched samples. Depending on the number and nature of the detected SNVs, it may be appropriate to filter the results in order to keep only those located in exon junctions, or those leading to nonsynonymous changes. Moreover, germinal DNA will be taken as a control to assess background noise, and establish sample-specific thresholds for SNVs to be accepted. Identified and confirmed SNVs will be annotated with broadly-used tools such as SIFT, Variant Effect Predictor, or MutationAssessor. Finally, self-contained pathway and functional analyses will be applied to the obtained results, in order to check that a specific pathway has different genomic or expression patterns between compared samples. The high throughput sequencing raw data will be stored as clinical research files for further reevaluations. All reference genomic files containing the genes, transcripts, and annotated mutations will be used as the control genomic profile of each sample.

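### The optional Picard duplicate-removal step does not suit the plan's amplicon assays: if applied without molecular barcodes it would discard most genuine reads and create false discordance between tissues

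*Protocol article*

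**What the plan says.** Three statements in the Methods of the Protocol article bear on this.

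- **Assay** (Biobanking and Sample Analysis): "Fully customized amplicon-based assays will be used" for the pathway genes. Targeted deep sequencing covers plasma, tumour and CTC DNA, and leukocyte DNA is assayed for each patient. Molecular barcodes are not mentioned. The techniques are referred to three cited proof-of-concept methods.
- **Depth** (Sample Size and Statistical Analyses): "Setting 3000x as the sequencing depth and 0.4 as the coefficient of variation", from which "we estimate there is enough statistical power (80%) to detect effects higher than 1.29".
- **Pipeline** (same section, bioinformatics paragraph): if necessary, "duplicate reads will be marked with Picard and removed before single nucleotide variation (SNV) identification". The article does not say what would make the step necessary and does not exempt amplicon data. The callers are meant to find low-frequency variants.

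The primary objective (Study Design and Objectives) is concordance of mutations between primary tumour and metastasis.

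**The concern.** Position-based duplicate marking treats reads with the same alignment ends as copies of one molecule. That is sensible when DNA is sheared at random, because two independent molecules rarely share both ends. In an amplicon library the primers set both ends, so all molecules from one amplicon share them. The tool then cannot separate PCR copies from independent molecules and keeps roughly one representative per distinct set of ends.

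Two things are at stake. Deep sequencing is used here to find low-frequency variants, and that ability disappears when only a handful of reads remain. The primary endpoint is also a comparison between tissues. If each tissue is represented by a few arbitrarily retained reads, a variant present in both will often be seen in only one. That artefact points the same way as the hypothesis in the Discussion, that primary tumours and metastases differ. The comparisons with cfDNA and CTCs are exposed in the same way.

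**Working it through.** **Inputs.** From the article: depth 3000x, coefficient of variation (CV) 0.4, power 80%, effect 1.29, 40 patients with complete data. Assumed because not stated: two-sided alpha 0.05; 40 samples per group (one primary and one metastatic sample per patient); 1 to 10 reads surviving per amplicon after coordinate-based removal, that is, 99.97% to 99.67% of 3000 reads removed.

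**Step 1: reproduce the plan's figure.** With the five factors the article lists, detectable fold-change = exp{√[2(z₀.₉₇₅ + z₀.₈₀)²(1/depth + CV²)/n]}.

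- 2(1.960 + 0.842)² ≈ 15.70
- 1/3000 + 0.16 = 0.1603
- 15.70 × 0.1603 / 40 = 0.0629, square root 0.251, exponential 1.285

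This agrees with 1.29. Solved the other way, 1.29 needs 38.8 (39) per group, and power at 40 per group is 81.2%.

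**Step 2: effect of depth on that figure.** CV² = 0.16 dominates 1/depth until depth is small.

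| Depth | Detectable fold-change | Power at 1.29 |
|---|---|---|
| 3000 | 1.285 | 81% |
| 300 | 1.288 | 81% |
| 100 | 1.295 | 79% |
| 30 | 1.317 | 74% |
| 10 | 1.376 | 61% |
| 4 | 1.494 | 43% |
| 2 | 1.664 | 29% |
| 1 | 1.963 | 18% |

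The power statement survives a thirty-fold loss of depth. It fails only under a collapse to a few reads.

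**Step 3: effect of depth on seeing a variant.** For allele fraction v and d reads, P(at least one mutant read) = 1 − (1 − v)^d.

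| Reads | v = 1% | v = 5% | v = 20% |
|---|---|---|---|
| 3000 | ~100% | ~100% | ~100% |
| 10 | 9.6% | 40% | 89% |
| 4 | 3.9% | 19% | 59% |
| 2 | 2.0% | 10% | 36% |
| 1 | 1% | 5% | 20% |

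One mutant read is a lenient standard. With at least three required, a 1% variant is found about 100% of the time at 3000 reads and about 0.01% of the time at 10.

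**Step 4: artefactual discordance.** Take a variant present at the same fraction in both tissues and seen in each with probability p. It appears in exactly one tissue with probability 2p(1 − p).

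- v = 30%: at 2 reads p = 1 − 0.7² = 0.51, giving 2 × 0.51 × 0.49 = 50%; at 10 reads p = 1 − 0.7¹⁰ = 0.972, giving 2 × 0.972 × 0.028 = 5%.
- v = 5%: at 2 reads p = 0.0975, giving 2 × 0.0975 × 0.9025 = 18%; at 10 reads p = 0.401, giving 2 × 0.401 × 0.599 = 48%.

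At 3000 reads p is essentially 1 in each case and this source of discordance vanishes. The fraction most affected depends on how many reads survive, but within the assumed range there is always a band of variants that would look discordant by chance.

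**The case against.** The strongest reply is that the plan does not commit to the step. The sentence opens with a condition, and the paragraph around it is a list of candidate tools and optional steps. A competent analyst would recognise primer-defined reads and skip removal. This stands: a reader might infer that the plan prescribes duplicate removal, and it does not. A reader might also infer that the condition gives no protection, because amplicon data always show a high apparent duplicate rate. The article names no rate and no trigger, and a very high rate could equally warn the analyst off.

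Second, the size of the loss depends on laboratory details that are not shown. Barcoding, fragmentation after amplification or heavy tiling would each leave more reads, and the cited methods are not at hand. This stands too. A collapse to one or two reads is a possibility under assumptions, not a fact about this study.

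Third, it is tempting to say that removal would destroy the 3000x on which the power calculation rests. Step 2 shows that this calculation is nearly indifferent to depth above about 100x. The article ties no minimum depth to low-frequency calling either, though that is where depth matters.

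Fourth, a collapse in depth would show in any coverage check, raw reads are kept for re-evaluation, and the sequencing analyses are declared exploratory. These points limit the harm to something recoverable, provided somebody looks.

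Finally, nothing says that duplicates would be removed in some sample types and not others. The wording merely leaves that open.

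These replies do not remove the point. A condensed article may leave the criterion for an optional step to a fuller document. Here, however, it names a specific step that is unsuited to the assay it also names.

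**Conclusion.** The concern holds in conditional form. If coordinate-based duplicate removal is applied to unbarcoded, unfragmented amplicon libraries, most genuine reads are lost. With 1 to 10 surviving reads per amplicon, the chance of seeing a 5% variant at all drops from about 100% to 5–40%, and a variant shared by both tissues can appear in only one of them up to about half the time. The stated effect of 1.29 reproduces (1.285) and is affected only below about 100x, so this is a problem for variant detection and concordance more than for the power statement.

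The conclusion rests on three things: Picard's use of alignment position, the absence of any mention of barcodes, and the assumed number of surviving reads. It should be corrected before sequencing. It is not evidence that the results will be invalid.

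**What to change.** In the bioinformatics paragraph of Sample Size and Statistical Analyses, replace the conditional step with a statement such as: coordinate-based duplicate removal will not be applied to the amplicon libraries; if reads are deduplicated, this will use molecular barcodes only and will be done identically for all sequenced sample types (primary tumour, metastasis, plasma, CTCs and leukocytes). Leukocytes belong in the list because germline DNA sets the background thresholds for accepting variants.

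Stating a minimum depth after filtering would also be useful. Primer trimming and restricting Picard to quality metrics are optional and not needed to cure this point.

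The cost is one sentence. The Results section reports that none of the 41 complete sample sets had been extracted or sequenced, so nothing would need to be redone.

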### Genomic Alterations in Primary Tumors Versus Metastases

An increasing number of studies have identified the existence of genetically distinct clonal subpopulations in some primary tumors [12]. Breast cancers have been classified by means of microarray-based comparative genome hybridization in single cells as either monogenomic or polygenomic, the latter having several clones that are evident in the primary tumor; polygenomic diagnoses carry a poorer prognosis [13,14]. Individual breast cancer tumor cell clones may harbor unique genetic alterations in addition to the founder mutations [15,16]. Distinct populations of breast cancer cells appear to interact in a competitive manner, both in the primary tumor and the micrometastatic environment. The selective pressure of therapeutic interventions can allow resistant cell clones to persist (usually as *dormant* cells) in distant organs. For unknown reasons these clones may expand, first in a silent way and later generating overt metastases, usually several years after the primary diagnosis. A substantial number of subdominant somatic mutations present in the primary tumor can evolve to become dominant in metastatic sites due to a selection process that is a consequence of the therapy [8,10]. Thus, the biology of metastases may be quite different from that of the primary tumor. This phenomenon can be particularly relevant in tumors that relapse after adjuvant treatments, especially if the relapse occurs years after the removal of the primary tumor.

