### Study Procedures

After the patient is enrolled, baseline demographic characteristics, medical history, and a complete physical examination will be recorded, and metastatic tissue and blood specimens will be obtained. Additionally, a paraffin block of the primary tumor tissue will be obtained and archived. Investigators will be trained in the specimen collection protocol of the Translational Oncology Research Unit of UHGM for the genomic studies. Biopsies of both the metastatic tissue and the blood sample must be taken close together in time; if the metastatic tumor tissue is obtained by puncture, the blood sample must be taken no more than 15 days before or after the biopsy. If the biopsy procedure is surgical, a peripheral blood sample must be taken on the same day as (or the day before) the biopsy procedure. Biopsy procedures will be guided using imaging technology as per clinical practice, unless metastasis is cutaneous. The biopsied tissue will then be formalin-fixed and sent for examination by the Pathology Service of the participating hospital. Whenever possible, a separate sample of the tissue will be sent directly to the Translational Oncology Research Unit of UHGM within 24 hours.

At the time of the biopsy, an assessment of any adverse events (AEs) possibly related to the biopsy procedure will be recorded. Those patients who do not return for a biopsy follow-up visit will be contacted by telephone for an AE safety evaluation during the 20 days following their most recent biopsy procedure. All AEs suspected to be related to the biopsy procedure will be followed up weekly, or as clinically indicated, until resolution or stabilization.

Patients (or parents/guardians in the case of disabled participants) may voluntarily withdraw from the study or be lost to follow-up, and patients may be dropped from the study at the discretion of the investigator at any time.

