### Biobanking and Sample Analysis

All specimen analyses will be performed at the laboratory of the Translational Oncology Research Unit of UHGM. For each patient, five types of biological samples will be obtained and analyzed, namely FFPE from primary tumor, FFPE from one metastatic site, plasma, white blood cells (WBCs), and CTCs. Parameters to be studied in each specimen are shown in Table 1.

**Table 1 table1:** Genomic studies per sample and specimen.

Specimen	Sample	Study	Biobanking
Formalin-fixed paraffin-embedded primary tumor	Tissue section	Immunohistochemistry for ER/PR, HER2, P53, Ki67	Formalin-fixed paraffin-embedded block
	DNA	Mutation profile and copy number variation	DNA
	RNA	PAM50 intrinsic subtype	Aliquot for RNA sequencing
Formalin-fixed paraffin-embedded metastases	Tissue section	Immunohistochemistry for ER/PR, HER2, P53, Ki67	Formalin-fixed paraffin-embedded block
	DNA	Mutation profile and copy number variation	DNA
	RNA	PAM50 intrinsic subtype	Aliquot for RNA sequencing
White blood cells	DNA	Mutations and copy number variation in germinal line	DNA
Circulating tumor cells	Circulating tumor cells	Number	DNA
	RNA	PAM50 intrinsic subtype	Aliquot for RNA sequencing
	DNA	Mutation profile and copy number variation	DNA
Plasma	Circulating free DNA	Quantification, mutation profile, and copy number variation	DNA

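### SNV noise thresholds are set from unfixed leukocyte DNA, which cannot show the fixation artefacts of the two FFPE tissues being compared

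*Protocol article*

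**What the plan says.** The sequencing part of Sample Size and Statistical Analyses states that "germinal DNA will be taken as a control to assess background noise", and gives the same control a second job: to "establish sample-specific thresholds for SNVs to be accepted". The pipeline is meant to find low-frequency variants.

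Biobanking and Sample Analysis gives the source of the control: for each patient, "genomic DNA from normal peripheral blood leukocytes will be assayed". On handling it says "Blood collected in ethylenediaminetetraacetic acid tubes will be processed within one hour to separate plasma, WBCs, and CTCs", and then "Samples will be frozen at -80ºC until the nucleic acids extraction is scheduled". No fixation step is described for any blood fraction.

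The same section lists the five specimens: "FFPE from primary tumor, FFPE from one metastatic site, plasma, white blood cells (WBCs), and CTCs". Both tumor tissues are therefore formalin-fixed and paraffin-embedded (FFPE). Under Study Procedures the metastasis is biopsied and fixed within the study, while for the primary "a paraffin block of the primary tumor tissue will be obtained and archived". The age of that block is not given.

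**The concern.** A patient's leukocyte DNA is a sound control for germline variants and for noise shared by every sample on the assay, such as PCR and sequencing error. It is not a sound measure of noise that arises only in fixed tissue. Formalin fixation and storage can add low-level base changes, mainly C>T/G>A. This is general laboratory knowledge and not a figure from the article. DNA that was never fixed does not carry those changes, so a threshold calibrated on it is too lenient for FFPE tumor DNA.

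The primary objective is the concordance of mutations between primary and metastasis. An accepted artefact present in only one block is counted as a private mutation of that block. An artefact in either tissue that is absent from blood also enters the list of tissue mutations that cfDNA and CTC-DNA appear to miss, which touches the secondary objective on liquid biopsy. Recruiting more patients does not remove either bias.

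**Working it through.** **The plan's own figure.** The article gives no artefact or error rate. Its one power calculation (depth 3000x, coefficient of variation 0.4, 80% power, effect 1.29, 40 patients) concerns count data. With two-sided 5% assumed, n = 2(1.960 + 0.842)²(1/3000 + 0.4²)/(ln 1.29)² = 38.8, so it is close to the stated 40. It says nothing about false SNV calls.

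**Step 1: what the control can see.**

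| Source of a false or irrelevant call | In leukocyte DNA? | In FFPE tumor DNA? |
|---|---|---|
| Germline variant | yes | yes |
| PCR or sequencing error | yes | yes |
| Fixation or storage damage | no | yes |

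The third row is the gap.

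**Step 2: how a threshold behaves when the tumor is noisier than the control.** All error rates here are assumed. Take 3000 reads, a leukocyte error of 0.1% per site, and a read threshold set from the binomial upper tail at that error. The table gives the probability that a site with no variant passes when tumor error is a multiple of leukocyte error.

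| Tail | Threshold | 2x | 3x | 5x |
|---|---|---|---|---|
| 0.001 | 11 reads (11/3000 = 0.37%) | 0.043 | 0.29 | 0.88 |
| 0.00001 | 14 reads (14/3000 = 0.47%) | 0.004 | 0.074 | 0.64 |

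With equal error (1x) and the 0.001 tail the pass rate is 0.0003. Over leukocyte errors of 0.05% to 0.2% and both tails, the 3x value runs from 0.017 to 0.71. The article states neither this threshold rule nor the number of panel positions, so these rates cannot be turned into artefacts per patient. The thresholds lie below 0.5% allele fraction, and a floor of a few percent would remove many such calls.

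**Step 3: patient level.** Let λ be the mean number of accepted, non-recurring artefacts per tissue pair (assumed, Poisson). Suppose that one private call makes a patient discordant, a definition the article does not give. The share of truly concordant patients mislabelled is 1 − exp(−λ):

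- λ = 0.1: 10%
- λ = 0.25: 22%
- λ = 0.5: 39%
- λ = 1: 63%

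**Step 4: mutation level.** Assume 3 shared mutations and 1 private mutation on each side, so concordance is 3/5 = 60%. One private artefact in the primary and an average of 0.5 in the metastasis give 3/6.5 = 46%. Two and one give 3/8 = 38%.

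**Step 5: direction.** An artefact found in both blocks counts as shared. With S shared out of T true mutations, adding k artefacts of which a fraction r recur gives (S + rk)/(T + k). This is below S/T only if r < S/T. In the example, one recurring artefact gives 4/6 = 67%, above 60%. The bias is towards discordance as long as fewer than 60% of the artefacts recur. Damage arising separately in two blocks should satisfy that; errors tied to a position might not.

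**The case against.** The best defence is that the leukocyte control is one step among several in a condensed article. Matched-sample callers, optional recalibration and filtering are also named, SNVs are to be confirmed before annotation, and profiling follows cited methods whose error models are not visible here. The Results section expects some tissue samples to be rejected on DNA quantity and quality, and the pathologist aims for areas above 70% cellularity, so mutations of the main clone should stand well above low-level noise. The analyses are declared exploratory, and raw data are kept for re-evaluation.

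Part of this stands. A remedy may exist in the full protocol, the worst blocks may be screened out, and calls can be refiltered later. But the optional filters described (exon junctions, nonsynonymous changes) do not target fixation damage, no confirmation step is described, and no allele-fraction floor is given. Thresholds specific to each sample do not help if they are derived from a control without the damage. The point concerns a control that the article positively names, so it is not a complaint about missing detail. Exploratory status does not excuse a systematic error in the primary objective.

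A further objection is sound and shapes the fix. A background built from other patients' tumor samples could absorb true recurrent mutations, because the panel covers pathways that are commonly altered.

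**Conclusion.** The concern holds in a limited form. As written, thresholds for fixed tissue come from unfixed DNA, so fixation artefacts can be accepted. Where they do not recur in both blocks, they bias the primary comparison towards discordance and lower the apparent sensitivity of cfDNA and CTC-DNA. The 10% to 63% range is an illustration that rests on the assumed λ and on one private call making a patient discordant. It is not an estimate for this study.

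Three stronger readings are not supported:

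- **That nearly all artefacts are private.** The article gives no basis for this, and recurring ones would count as agreement (Step 5).
- **That older primary blocks carry more noise and so produce a spurious excess of lost mutations.** The remark that overt metastases appear "usually several years after the primary diagnosis" is background on dormant clones. Patient Selection sets no interval and block ages are not stated, so a difference in noise is possible but not shown.
- **That the leukocyte control is useless or was wrongly collected.** It remains right for germline removal and common assay noise.

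This is a cheap improvement worth making before sequencing. The article reports that none of the 41 complete sample sets had yet been extracted or sequenced.

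**What to change.** 1. Keep leukocyte DNA for removing germline variants and for noise common to the assay.
2. Set SNV acceptance thresholds by specimen type. For FFPE, use an error estimate by substitution type, and by position where feasible, with a higher allele-fraction floor for C>T/G>A.
3. If other patients' FFPE samples supply that background, leave out high-fraction calls and known hotspot positions so that true recurrent mutations are not absorbed into the noise.
4. Report primary-metastasis concordance with and without low-fraction C>T/G>A calls, and descriptively by age of the primary block.

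The cost is extra bioinformatics work on data already planned, the recording of block age, and some loss of sensitivity for low-fraction C>T/G>A variants in FFPE. No new specimens are needed.
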